### Outcome measures

#### Participant-level outcome measures

Participant-level outcome measures were measured at 12 weeks and 26 weeks post-injury, as outlined in the schedule in Table 1 (above). These include EuroQoL-5D-3L [17], mRS [18], FIM [19], HADS [21] and the Modified Caregiver Strain Index [20]. The mRS [18] score will be dichotomised into independent (0–2) or dependent / dead (3–6) and reported as a binary variable. Frequencies and percentages of the mRS [18] categories will be reported by trial phase (control/intervention). All other outcome measures will be treated as continuous; for these measures, the mean score will be reported together with the standard deviation.

#### System-level outcome measures

The median and IQR will be reported for occasions of service by trial phase (control/intervention).

##### Minimum processes of care (MPC)

The trial protocol lists twelve processes or care, not all of which are applicable to all participants (e.g. not all participants will require an interpreter). The achievement of minimum processes of care (MPC) is defined as the achievement of at least 80% of all process of indicators that are applicable to a participant. The achievement of MPCs will be reported as a binary variable (achieved/not achieved) at 12 and 26 weeks post-injury. Frequencies and percentages by trial phase (control/intervention) will be reported.

Details of how these outcomes will be presented are outlined in Table 4 (12-week outcomes) and Table 5 (26-week outcomes) of Appendix.

### Analysis of primary outcome

#### The primary effectiveness hypothesis states

Compared to UC, implementation of the proposed intervention package (IP) will result in a higher score on the Euro QOL–5D-3L [17] VAS at 26 weeks post-injury.

#### Analysis

A mixed effects linear regression model will be used to assess the between-group difference on Euro QOL–5D-3L [17] VAS score at 26 weeks post-injury. The model will control for injury type and severity (dichotomised mRS [18] at baseline), age at recruitment and time period (time since commencement of the trial) as fixed effects; recruitment site and participant/individual will be included as random effects. The treatment effect will be reported as the mean difference between the intervention condition and the control condition, together with the 95% confidence interval for the difference.

### Treatment of missing values

The primary analysis will be reported without imputation of missing data. If the amount of missing data warrants imputation (i.e. the number of missing values on the primary outcome measure exceeds 10%), missing data imputation will be conducted under the assumption that missing values are missing at random (MAR) [35]. That is, it is assumed that the values of the missing data may reasonably be predicted from all observed data. In particular, it will be assumed that missing values of the primary outcome measure (Euro QOL–5D-3L [17] VAS at 26 weeks post-injury) may be estimated from variables on which data has been collected (e.g. injury type, baseline injury severity, baseline mRS [18], age, gender, site, minimum processes of case, Euro QOL–5D-3L [17] VAS at 12 weeks post-injury), and on the observed values of Euro QOL–5D-3L [17] VAS at 26 weeks post-injury. To ensure robustness of the imputation, 20 imputed data sets will be generated with a separate model being developed for each imputation. These multiple imputations will be conducted using chained Eqs. [36, 37]. The pooled result of these imputed models will be reported and compared with the primary model (without imputed data).

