### Sample size

Our sample size estimation procedure involved three steps. In the first step, we conducted a naïve sample size estimation which ignored the clustering effects of data collected through the stepped wedge design. In the second step, we calculated the design effect of the stepped wedge, using the method presented by Woertman et al. [27]. We then calculated the total sample size required by multiplying the naïve sample size calculated in the first step by the design effect and the total number of time periods in the planned design.

Our estimation was based on our primary outcome measure of Euro QOL–5D [17] VAS. We did not have any studies or preliminary data on the use of this measure in Aboriginal Australian populations. Therefore, our estimate of the effect of the intervention was based on the mean difference on the Euro QOL–5D [17] VAS between stroke and non-stroke populations in the published literature. Based on the literature [28, 29], the mean difference between stroke and non-stroke populations on the Euro QOL–5D [17] VAS was approximately 25 points with a standard deviation of 25. Guided by this information, we assumed that the intervention would result in an improvement of 15 points on the Euro QOL–5D [17] VAS (with a standard deviation 25), which equates to a standardised effect size of d = 0.6 for an independent sample t-test.

Using GPower 3.1 [30], we estimated the naïve sample size for an independent samples t-test and calculated that we would require a total of 90 participants to detect our estimated difference of d = 0.6 with 80% power at the 5% significance level.

The design effect proposed by Woertman et al. [27] is based on the number of clusters, number of steps, number of measurements at the end of each step and number of baseline measurements. Our proposed design had four clusters which were randomised to commence intervention in four steps, one baseline measurement and one measurement at the end of each step. We assumed a conservative intraclass correlation of 0.08. Based on these inputs, we calculated a design effect of 0.56. Multiplying the naïve sample size (n = 90) by the design effect (DEsw = 0.56) and the number of time periods in the trial (n = 24), and rounding-up our results to ensure that the number of patients per cluster per time period was an integer, we obtained a total sample size of 312 or 13 per cluster per time period.

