## Statistical analysis plan

### Analysis principles and general considerations

All outcomes and analyses were prospectively characterised as primary or secondary.This is a superiority trial with intervention expected to yield superior outcomes, compared to control. However, all outcomes will be tested independently at the two-tailed 5% significance level. All estimates of treatment effects will be presented with 95% confidence intervalsNo formal adjustments will be undertaken to constrain the Type I error associated with planned secondary or exploratory analyses. The information provided by analyses is designed to supplement the evidence from the primary analyses; it will provide a more complete characterisation of the treatment effects.The analyses for all quantitative outcome measures will be conducted on an intention the treat (ITT) basis, i.e. all participants will be analysed in the trial phase (control or intervention) in which they were recruited, regardless of whether their treatment adhered to the trial protocol or not. The ITT strategy for this trial is based on the following principles:◦ All available outcome data are collected on all recruited participant◦ For the ITT analysis, the outcomes for each participant will be included in the data for the trial phase (control/intervention) in which the participant was recruited.◦ All available outcome data will be used in the primary analyses. The primary analyses will be reported without imputation of missing data. If the amount of missing data exceeds 10% at the primary endpoint, missing data will be imputed under the assumption that data is missing at random.◦ A sensitivity analysis including all randomised individuals will be conducted. The sensitivity analysis will consider alternative assumptions about data missing not at random (MNAR).For primary and secondary analyses, the treatment effects for the participant-level effectiveness outcomes will be adjusted for brain injury type (stroke or TBI) and severity of injury (mRS) [18] at baseline. In addition, age at recruitment, timepoint (time since injury) and time period (6-month block of time in which the participant is recruited to the step-wedge trial) will be included as fixed effects. Hospital site will be included as a random effect. Unadjusted analyses will be reported separately from these pre-specified analyses.All analyses will be conducted using the R Statistical Programming Language [32] after data collection is completed and the database is locked.

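### The plan does not settle whether the H1 model uses the 12-week VAS, and the imputed result that does use it is given no deciding role

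*SAP article*

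**What the plan says.** **Model for H1.** Under Analysis of primary outcome, a linear mixed model compares conditions on the VAS at 26 weeks. On fixed effects: "The model will control for injury type and severity (dichotomised mRS [18] at baseline), age at recruitment and time period". Site and participant are random effects. Time since injury and its interaction with condition are not listed.

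**General rule.** Analysis principles and general considerations lists timepoint among the fixed effects for primary and secondary analyses, and says: "All available outcome data will be used in the primary analyses".

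**Missing data.** The primary analysis is reported without imputation. Imputation starts on a condition: "If the amount of missing data warrants imputation (i.e. the number of missing values on the primary outcome measure exceeds 10" per cent). It assumes that missing 26-week scores can be predicted from observed data, with the 12-week VAS, gender and processes of care among the examples. On the role of the imputed estimate: "The pooled result of these imputed models will be reported and compared with the primary model (without imputed data".

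**Related text.** The 12-week VAS is otherwise descriptive only (Secondary participant-level outcome measures). Sensitivity analyses adds a delta adjustment for data missing not at random; if plausible deltas overturn the inference, the result is called equivocal. If a model still fails to converge after effects are dropped, separate models at each timepoint may be used (Effect of lower sample size on statistical analysis plan).

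**The concern.** The H1 estimate depends on a choice that the plan leaves open. With 26-week values only, the primary analysis conditions on less than the plan's own missing-at-random assumption does, and a participant with only a 12-week VAS contributes nothing. With both visits but no condition-by-time term, the condition coefficient is not a 26-week effect. In either case the imputed estimate is reported beside the primary one, with no statement of which decides H1 if they disagree. Loss that differs by condition is plausible, because only intervention participants have monthly coordinator contact (The intervention). At stake are the size of the headline effect and whether the route to it is fixed before the data are seen.

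**Working it through.** **1. The two readings side by side.**
- *26-week only:* the H1 model is written for the 26-week score and lists neither time since injury nor the interaction. The mixed models for occasions of service, processes of care, mRS, FIM and HADS each add both terms explicitly. The 12-week VAS is called descriptive.
- *Both visits:* a participant random effect cannot be separated from residual error with one VAS per person. The general rule includes timepoint for the primary analysis. Separate models by timepoint are a fallback, which implies a joint default.

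The text does not decide between them.

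**2. Inputs from the SAP.** Test: "all outcomes will be tested independently at the two-tailed 5% significance level". Target: "we assumed that the intervention would result in an improvement of 15 points on the Euro QOL–5D [17] VAS (with a standard deviation 25"). Check: 15/25 = 0.6, and a noncentral t calculation gives a total of 90 with 80.4% power, matching "we would require a total of 90 participants to detect our estimated difference of d = 0.6 with 80% power at the 5% significance level". Clustering: "We assumed a conservative intraclass correlation of 0.08". Recruited: 108. The SAP gives no figure for bias in H1.

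**3. Assumptions (not in the SAP).** Correlation r of the 12- and 26-week VAS: 0.6, range 0.5 to 0.7. Loss at 26 weeks: varied below. Number of controls: 45 to 63.

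**4. 26-week values only.** If one condition loses its lowest fraction m on the 12-week VAS and the other loses none or loses at random:

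bias = r × SD × g(m), with g(m) = φ(z_m)/(1 − m).

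For m = 0.20 and r = 0.6: g = 0.280/0.80 = 0.350, so 0.6 × 25 × 0.350 = 5.25 points, or 35% of 15.

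| Loss pattern | Size of bias, r = 0.5 to 0.7 |
|---|---|
| Sharp selection, one condition, 10% | 2.4 to 3.4 |
| Sharp, one condition, 20% | 4.4 to 6.1 |
| Sharp, one condition, 30% | 6.2 to 8.7 |
| Graded (odds ratio 3 per SD), one condition, 20% | 2.3 to 3.3 |
| Graded, one condition, 30% | 3.4 to 4.7 |
| Same graded mechanism, 10% v 20% | 1.1 to 1.5 |
| Same sharp mechanism, 10% v 20% | 1.9 to 2.7 |
| Same sharp mechanism, 10% v 30% | 3.8 to 5.3 |
| Same mechanism, equal loss | 0 |

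Selective loss in control pulls the estimate down; selective loss in intervention pushes it up.

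*Worked scenario.* True effect 15. Control loses 36% (odds ratio 3.3 per 25 points lower at 12 weeks); intervention loses 10% at random; r = 0.6. In a large sample the 26-week-only estimate is 10.0, a bias of 10.0 − 15 = −5.0. Imputation with 12-week VAS and condition gives 15.0. A simulation of 2,500 trials with N = 108 and intraclass correlation 0.08 (least squares with pair and period effects) gave means of 9.8 and 14.5, with power 15% and 27%. With the same mechanism in both conditions (28% v 19% lost) it gave 14.3 un-imputed and 15.4 imputed, so neither is more than 1 point from 15.

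**5. Both visits, no interaction.** With complete data and equal variances the condition coefficient is the average of the two effects. If the true effects are 10 at 12 weeks and 15 at 26 weeks, this is (10 + 15)/2 = 12.5; with 7.5 at 12 weeks, (7.5 + 15)/2 = 11.25. Under the loss in the worked scenario the values fall to about 12.0 and 10.5. The model recovers 15 only if the two effects are equal.

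**6. Both visits with condition-by-time.** The 26-week contrast in the worked scenario is 15.0. Across the other loss patterns simulated, bias was between about −0.9 and +1.0, compatible with zero given simulation noise.

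**7. The trigger.** 10/108 = 9.3% does not exceed 10%. If all 10 are controls, control loss is 10/63 = 16% to 10/45 = 22%. If each would have scored 15 points below those retained, the observed control mean is too high by 15 × 10/63 = 2.4 to 15 × 10/45 = 3.3 points.

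**The case against.** The strongest reply is that the model was meant to use both visits. The participant random effect, the timepoint term and the all-available-data principle support that, and a joint model with the interaction needs no imputation to be valid under missing at random. This stands as far as it goes: a reader might infer that H1 is certainly a complete-case analysis at 26 weeks, and the SAP does not establish that. But the model that rescues H1 contains a condition-by-time term, which neither the primary-outcome section nor the general rule specifies for the VAS.

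Second, the numbers are chosen. The SAP states no loss rates beyond a 4% drop-out allowance and no correlation, and the N = 108 simulation omits baseline covariates that could absorb part of the selection. This also stands. A reader might take a third of the target as a ceiling, or conclude that the plan's own assumption declares the primary analysis biased. Neither follows. The bias runs from 0 to more than half the target (8.7/15 = 58%) according to what is assumed. The missing-at-random statement says that missing scores are predictable from observed data, not that loss depends on the 12-week VAS differently by condition.

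Third, an un-imputed primary analysis fixed in advance, with imputation beside it and a delta rule behind it, is a recognised arrangement. That is fair. However, the delta rule concerns departures from missing at random. It does not say which missing-at-random estimate decides H1, and the plan leaves unclear whether it runs below the 10% trigger.

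**Conclusion.** The point holds as an unsettled specification with a possible cost, not as a demonstrated bias. As written, the H1 model either ignores the 12-week VAS or, if it uses both visits, lacks the term that isolates the 26-week effect. On the first reading the estimate could be off by about 5 of 15 points under 36% selective control loss, 10% random intervention loss and correlation 0.6, all assumed. It would be off by about 0 to 1 point when the same mechanism acts in both conditions at similar rates. On the second reading an estimate of about 12.0 or 10.5 instead of 15 would follow if the true 12-week effect were 10 or 7.5 under the same loss. The imputed result has no deciding role, and the pooled trigger can miss loss concentrated in one condition; both follow directly from the text. The matter should be corrected before lock. Imputation need not become the headline, because a properly specified joint model does the same job.

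**What to change.** Before database lock:

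1. In Analysis of primary outcome, state that H1 is fitted to both VAS visits with time since injury and condition-by-time, as for the secondary outcomes modelled this way, and that the 26-week contrast is the H1 result.
2. State that if this model does not converge and the 26-week-only fallback is used, the pooled multiple imputation, with 12-week VAS and condition in the imputation model, decides H1.
3. In Analysis principles and Treatment of missing values, delete the 10% trigger, so that imputation and the delta analysis run whenever any 26-week VAS is missing.

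The cost is a few sentences and slightly more analysis work, with data and methods already planned. The H1 result then depends somewhat on the joint or imputation model. When little is missing, the 26-week contrast, the imputed result and the un-imputed 26-week analysis nearly coincide.

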### Sensitivity analyses

The imputation of missing values of the primary outcome is planned under an assumption of missing at random (MAR); therefore, a sensitivity of the results will be conducted to explore plausible departures from MAR.

The 2010 National Research Council Panel on the Handling of Missing Data in Clinical Trials [35] recommended a transparent and easily interpretable method for conducting a sensitivity analysis. Specifically, it recommended adding a parameter (delta) to the mean response. The parameter, delta, measures the degree of departure from missing at random. We propose using this approach to conduct a sensitivity analysis that assesses sensitivity of the results to plausible departures from the MAR assumption in this trial. If the inference about the treatment effects can be overturned by plausible values of the delta parameter, then the results of the trial will be considered equivocal.

### Secondary statistical hypotheses

The secondary effectiveness hypotheses (H2–H5) yield the following statistical hypotheses:H2.1 Compared to usual care, implementation of the IP will result in increased occasions of service in the first 12 weeks post-injury.H2.2 Compared to usual care, implementation of the IP will result in increased occasions of service across the first 26 weeks post-injury.H3.1 Compared to usual care, implementation of the IP will result in an increased proportion of participants receiving at least the minimum processes of care in the first 12 weeks post-injury.H3.2 Compared to usual care, implementation of the IP will result in an increased proportion of participants receiving at least the minimum processes of care across the first 26 weeks post-injury.H4.1 Compared to usual care, implementation of the IP will result in an increased proportion of participants achieving independence as determined by mRS [18] at 12 weeks post-injury.H4.2 Compared to usual care, implementation of the IP will result in an increased proportion of participants achieving independence as determined by mRS [18] at 26 weeks post-injury.H4.3 Compared to usual care, implementation of the IP will result in increased FIM™ [19] at 12 weeks post-injury.H4.4 Compared to usual care, implementation of the IP will result in increased FIM™ [19] at 26 weeks post-injury.H5.1 Compared to usual care, implementation of the IP will result in lower scores on the Modified Caregiver Strain Index [20] at 12 weeks post-injury.H5.2 Compared to usual care, implementation of the IP will result in lower scores on the Modified Caregiver Strain Index [20] at 26 weeks post-injury.H5.3 Compared to usual care, implementation of the IP will result in lower anxiety as measured on the Hospital Anxiety and Depression Scale [21] at 12 weeks post-injury.H5.4 Compared to usual care, implementation of the IP will result in lower anxiety as measured on the Hospital Anxiety and Depression Scale [21] at 26 weeks post-injury.H5.5 Compared to usual care, implementation of the IP will result in lower depression as measured on the Hospital Anxiety and Depression Scale [21] at 12 weeks post-injury.H5.6 Compared to usual care, implementation of the IP will result in lower depression as measured on the Hospital Anxiety and Depression Scale [21] at 26 weeks post-injury.

### Analysis of secondary statistical hypotheses

#### Occasions of service

A linear mixed effects regression model will be used to assess between-condition differences on occasions of service [H2]. Time period, age at recruitment, injury type and severity (dichotomised mRS [18] at baseline) will be controlled for as fixed effects in the model. Recruitment site and participant/individual will be included as random effects. In addition, time since injury and the interaction of time since injury with condition (control/intervention) will be included in the model. The interaction effect will be used to assess the between-group differences at 12 weeks post-injury [H2.1] and at 26 weeks post-injury [H2.2].

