#### Processes of care

Minimum care processes [H3] will be dichotomised as achievement of minimum care processes (at least 80% of all applicable processes of care administered) versus non-achievement of minimum care processes. A mixed effects logistic regression model will be used to assess between-condition differences on this binary variable. Time period, age at recruitment, injury type and severity (dichotomised mRS^16^ at baseline) will be controlled for as fixed effects in the model. Recruitment site and participant/individual will be included as random effects. In addition, time since injury and the interaction of time since injury with condition (control/intervention) will be included in the model. The interaction effect will be used to assess the between-group differences at 12 weeks post-injury [H3.1] and at 26 weeks post-injury [H3.2].

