#### Stroke disability/injury severity

The score on the mRS [18] will be dichotomised as independent (mRS [18] 0–2) or dependent /dead (mRS [18] 3–6). A mixed effects logistic regression model will be used to assess between-condition differences on this binary variable. Time period, age at recruitment, injury type and severity (dichotomised mRS [18] at baseline) will be controlled for as fixed effects in the model. Recruitment site and participant/individual will be included as random effects. In addition, time since injury and the interaction of time since injury with condition (control/intervention) will be included in the model. The interaction effect will be used to assess the between-group differences at 12 weeks post-injury [H4.1] and at 26 weeks post-injury [H4.2].

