#### Functional independence

A linear mixed effects regression model will be used to assess between-condition differences on the Functional Independence Measure (FIM™) [19]. Time period, age at recruitment, injury type and severity (dichotomised mRS [18] at baseline) will be controlled for as fixed effects in the model. Recruitment site and participant/individual will be included as random effects. In addition, time since injury and the interaction of time since injury with condition (control/intervention) will be included in the model. The interaction effect will be used to assess the between-group differences at 12 weeks post-injury [H4.3] and at 26 weeks post-injury [H4.4].

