#### Caregiver strain

Data on the Modified Caregiver Strain Index [20] was obtained from 25 next-of-kin at 12 weeks post-injury and 21 next-of-kin at 26 weeks post-injury. Given the relatively small sample size for these data, differences in caregiver strain between the control and intervention phases of the trial will be assessed using independent samples *t*-tests. The *t*-tests will be conducted at the 5% significance level, and 95% confidence intervals will be reported. No additional modelling will be undertaken and no adjustments for any covariates will be made.

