#### Anxiety and depression

Separate linear mixed effects regression model will be used to assess between-condition differences on anxiety and depressions scales of the HADS [21]. Time period, age at recruitment, injury type and severity (dichotomised mRS [18] at baseline) will be controlled for as fixed effects in the models. Recruitment site and participant/individual will be included as random effects. In addition, time since injury and the interaction of time since injury with condition (control/intervention) will be included in the models. The interaction effect will be used to assess the between-group differences at 12 weeks post-injury [H5.3] and at 26 weeks post-injury [H5.4].

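### Five secondary analyses name the condition-by-time interaction as the test of the 12- and 26-week differences; under usual coding it tests only whether the effect changes

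*SAP article*

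**What the plan says.** The section on secondary statistical hypotheses lists 14 hypotheses. Each concerns a difference between conditions at, or up to, one time; H4.3, for example, states that "implementation of the IP will result in increased FIM™ [19] at 12 weeks post-injury".

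The analysis section for occasions of service lists the covariates and random effects and then adds: "In addition, time since injury and the interaction of time since injury with condition (control/intervention) will be included in the model". The test follows: "The interaction effect will be used to assess the between-group differences at 12 weeks post-injury [H2.1] and at 26 weeks post-injury [H2.2". The same sentence recurs for:

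- Processes of care: "The interaction effect will be used to assess the between-group differences at 12 weeks post-injury [H3.1] and at 26 weeks post-injury [H3.2"
- mRS: "The interaction effect will be used to assess the between-group differences at 12 weeks post-injury [H4.1] and at 26 weeks post-injury [H4.2"
- FIM: "The interaction effect will be used to assess the between-group differences at 12 weeks post-injury [H4.3] and at 26 weeks post-injury [H4.4"
- HADS: "The interaction effect will be used to assess the between-group differences at 12 weeks post-injury [H5.3] and at 26 weeks post-injury [H5.4". This paragraph covers separate anxiety and depression models but names only the anxiety hypotheses.

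Caregiver strain is handled differently: "differences in caregiver strain between the control and intervention phases of the trial will be assessed using independent samples" t-tests.

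The section on the effect of the lower sample size gives a last-resort fallback of separate models at 12 or 26 weeks, in which time since injury and its interaction with condition are called redundant.

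The article defines no timepoint contrast. It does not say whether time since injury is categorical or numeric, whether baseline is one of its levels, or whether condition also enters as a main effect.

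**The concern.** In a model with condition, time and their product, the interaction term measures how the treatment effect differs between visits. It does not measure the effect at either visit, and with two visits it is a single parameter, which cannot test two separate hypotheses.

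An analyst who follows the sentence under that coding could go wrong in two ways. A benefit of equal size at 12 and 26 weeks gives an interaction of zero and would be reported as no effect at either time. An effect present only at 26 weeks gives a non-zero interaction, which the rule would also credit to the 12-week hypothesis. Leaving the contrast undefined also leaves the choice of test open until after results are seen, which a plan approved before database lock is meant to prevent.

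**Working it through.** **1. Count.** The list holds H2.1–H2.2 (2), H3.1–H3.2 (2), H4.1–H4.4 (4) and H5.1–H5.6 (6), so 2 + 2 + 4 + 6 = 14. H5.1 and H5.2 use t-tests, leaving 12 that rest on the interaction sentence. By the labels printed in the analysis section it is 10, because H5.5 and H5.6 are not cited.

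**2. What the interaction is under each coding.** Let G = 1 for intervention, and let D12 and D26 be the between-condition differences at the two visits.

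- *Condition + time + interaction:* E(Y) = a + b·[26 wk] + c·G + e·G·[26 wk]. Then D12 = c, D26 = c + e and e = D26 − D12. In the logistic models, exp(e) is a ratio of two odds ratios.
- *The same with numeric time:* one coefficient per week, (D26 − D12)/14, which gives the same test.
- *Categorical time, no condition main effect:* E(Y) = a + b·[26 wk] + c12·G·[12 wk] + c26·G·[26 wk]. The two interaction coefficients are D12 and D26.
- *Baseline as a third level:* Table 1 makes this possible for mRS, FIM and HADS; Table 2 rules it out for occasions of service and processes of care. With a condition main effect, the two interaction coefficients are differences in change from baseline, which the hypotheses do not state.

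The algebra was checked on one simulated data set of 108 participants with a true effect of 0.6 at both visits. The raw differences were 0.4629 at 12 weeks and 0.7734 at 26 weeks. The first coding gave a condition coefficient of 0.463 (p = 0.011) and an interaction of 0.311 (p = 0.088), matching 0.7734 − 0.4629 = 0.3105. The third coding gave 0.463 and 0.773.

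**3. Which coding the text implies.** The paragraphs list time and the interaction but no separate condition term. The fallback, however, drops time and the interaction and still compares conditions. If condition entered only through the interaction, nothing would be left to test. The fallback therefore implies a condition main effect, which is the first coding.

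**4. Size.** The plan attaches no figure to the interaction test. The illustration borrows the effect assumed for the primary outcome: 15/25 = 0.6. The plan's unclustered total of 90 reproduces: the exact t-test at 45 per group has 80.4% power.

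Assumptions: 108 participants split 54/54, complete data, unit SD, no clustering or period effects, and a within-person correlation r of 0.3, 0.5 or 0.8. The documents give neither the split in the visible text nor r.

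- SE of a timepoint contrast = √(2/54) = 0.192
- SE of the interaction = √(2(1 − r)·2/54) = 0.228, 0.192 and 0.122

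Rejection rates at two-sided 5%, from 20,000 simulated trials; a range or list for the interaction covers the three values of r:

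| True effect, 12 wk / 26 wk | Interaction | 12-wk contrast | 26-wk contrast |
|---|---|---|---|
| 0.6 / 0.6 | 4.8–5.0% | about 87% | about 87% |
| 0 / 0.6 | 74%, 87%, 99.8% | about 5% | about 87% |
| 0.3 / 0.6 | 26%, 33%, 68% | about 34% | about 87% |

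**The case against.** The strongest reply is that the sentence assigns two separate differences to two numbered hypotheses, so its authors probably meant the timepoint-specific effects from a model that contains the interaction. The section on analysis principles speaks of a timepoint and promises treatment effects with confidence intervals. The terms literally listed omit a condition main effect, and with categorical time that model already yields the two differences.

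This stands in part. A reader might infer that the hypotheses are certain to be mis-tested and that no other reading is possible, even for occasions of service and processes of care. The documents do not support that, because the coding without a main effect is a valid reading and answers the right question. It needs two conditions that the plan never states, though, and the fallback speaks against one of them.

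A reader might also infer that a benefit fading by 26 weeks would be reported as benefit at 26 weeks. That does not follow: the interaction would have the opposite sign to benefit, and estimates with intervals are to be reported, so the error would require ignoring the sign.

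The power figures are also open to objection. They borrow a VAS effect for other outcomes, four of the 12 hypotheses use logistic models, and clustering and period adjustment would mainly lower the precision of the between-condition contrast. The 87% is therefore probably optimistic. The roughly 5% is not affected in the same way, since it is the false-positive rate of a test whose target is zero.

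**Conclusion.** The point holds as a mis-stated test. Under the usual coding, which the convergence fallback implies, the named interaction tests change in effect and not the stated hypotheses, for up to 12 of 14 secondary hypotheses. Whether they would in fact be mis-tested depends on a coding that the plan leaves open. Adding baseline as a level does not rescue the wording, because the hypotheses are not about change from baseline.

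The direction of the error follows from algebra alone. The rejection rates are illustrative, rest on the assumptions listed with them, and are not estimates of this trial's power.

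Severity is moderate. The primary analysis tests the 26-week VAS difference without this interaction, caregiver strain uses t-tests, and the plan presents its secondary analyses as supplementary to the primary.

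**What to change.** Keep the models and change the statement of the test.

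- State that time since injury is categorical, name its levels for each outcome, and state that condition enters as a main effect.
- Test each hypothesis by the model-based intervention-minus-control contrast at 12 weeks and at 26 weeks, with a 95% confidence interval: a mean difference for the linear models and an odds ratio for the logistic models.
- Report the interaction only as a test of whether the effect differs between visits.
- In the anxiety and depression paragraph, assign the anxiety contrasts to H5.3–H5.4 and the depression contrasts to H5.5–H5.6.

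The cost is one sentence per outcome in the plan and one contrast statement per model in the code. No further data are needed.
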